### Statistical approach

Our primary aim is to evaluate the effect of CR on cognition in patients with BDP compared to a computer-based control. The primary outcome measures of interest are MCCB scores. Primary analyses will be based on composite scores; secondary analyses will examine domain scores if composite findings are significant. The main analysis will be an intent-to-treat analysis, which includes all randomized subjects regardless of compliance to reduce potential for post-randomization bias and inflation of Type I errors. We will use a linear mixed effects model; inclusion of random effects accounts for the correlation among repeated measures. Outcome measures will include the three post-baseline measures of cognition; the baseline measure will be adjusted for by including it as a covariate. The test of no treatment difference will be based on a joint test of the group and group-by-time interaction.

The secondary aim is the examination of potential mechanisms for changes in community functioning. It is hypothesized that cognitive (but not clinical) change will mediate changes in community functioning. Thus, community functioning will be modeled adjusting for composite neuropsychological (or clinical) change using linear mixed effects models to relate changes in community functioning to treatment group while adjusting for differences in cognitive (or clinical) change.

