**Methods/Design:**

The Treatment to Enhance Cognition in Bipolar Disorder study is an investigator-initiated, parallel group, randomized, blinded clinical trial of an Internet-based cognitive remediation protocol for patients with bipolar disorder I with psychosis (*n* = 100). We also describe the development of our dose-matched active control paradigm. Both conditions involve 70 sessions of computer-based activities over 24 weeks. The control intervention was developed to mirror the treatment condition in dose and format but without the neuroplasticity-based task design and structure. All participants undergo neuropsychological and clinical assessment at baseline, after approximately 25 hours of study activities, post treatment, and after 6 months of no study contact to assess durability. Neuroimaging at baseline and post treatment are offered in an “opt-in” format. The primary outcomes are scores on the MATRICS battery; secondary and exploratory outcomes include measures of clinical symptoms, community functioning, and neuroimaging changes. Associations between change in cognitive measures and change in community functioning will be assessed. Baseline predictors of treatment response will be examined.

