Assessments are conducted at baseline, midpoint (after approximately 25 hours of training) post treatment (within 1 week of completing the treatment/control), and at follow-up (6 months after completion of the treatment/control). All subjects complete clinical and cognitive assessments; neuroimaging is presented as an “opt in” portion of the study. Clinical and cognitive assessments are typically conducted in the same session. Baseline assessments occur 2 weeks or less prior to the start of training; post-treatment assessments are conducted within 1 week of completing the final training session.

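### The community-functioning model gives a group effect adjusted for post-randomization change, which is neither the effect of CR on functioning nor, by itself, evidence that cognitive but not clinical change mediates it

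*Protocol article*

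**What the plan says.** All references are to the protocol article. Under Statistical approach, the secondary aim reads: "The secondary aim is the examination of potential mechanisms for changes in community functioning". The hypothesis follows: "It is hypothesized that cognitive (but not clinical) change will mediate changes in community functioning". The next sentence draws the analysis from it: "community functioning will be modeled adjusting for composite neuropsychological (or clinical) change using linear mixed effects models", in order "to relate changes in community functioning to treatment group while adjusting for differences in cognitive (or clinical) change".

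The same section gives a treatment comparison without a mediator for cognition only: "The test of no treatment difference will be based on a joint test of the group and group-by-time interaction", with the baseline score as covariate.

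The abstract gives functioning a standing of its own: "secondary and exploratory outcomes include measures of clinical symptoms, community functioning, and neuroimaging changes". It adds one more analysis that involves functioning: "Associations between change in cognitive measures and change in community functioning will be assessed". That is an association between two changes, not a comparison of the arms.

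On timing, Procedures schedules assessments at baseline, midpoint, post treatment and 6 months later, and notes: "Clinical and cognitive assessments are typically conducted in the same session".

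**The concern.** Two questions are served by one model, and it answers neither alone.

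- **Does CR improve functioning?** This needs the randomized comparison of the arms. Once cognitive change is a covariate, the part of the benefit that runs through cognition is removed from the group coefficient. The closer the trial's theory is to the truth, the nearer that coefficient lies to zero.
- **Does cognitive change mediate the benefit?** Cognitive change is not randomized. Mood, effort or general recovery can move cognition and functioning together and shift the group coefficient with no causal path between them.

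The claim of cognitive but not clinical mediation is also comparative. The wording enters the two changes as alternatives, so no quantity in the model compares them.

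At stake is the interpretation of the secondary aim. The Background section justifies CR largely by the hope that better cognition leads to better community outcomes. The section also chooses intent-to-treat for cognition in order to limit post-randomization bias, yet the functioning model conditions on a post-randomization variable.

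**Working it through.** **The plan's own figure.** Power calculation gives 80% power for an effect of 0.54 with 100 participants, 15% attrition and one-tailed alpha 0.05. Per arm, 50 × 0.85 = 42.5. Power = Φ(0.54 × √(42.5/2) − 1.645) = Φ(2.489 − 1.645) = 0.80. The figure reproduces. It concerns cognition and is used below only as a plausible cognitive effect.

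**Inputs for the illustration**
- Cognitive effect a = 0.54 SD (Power calculation).
- Total functioning effect c = 0.30, 0.50 or 0.80 SD. Assumed; the article gives none.
- Within-arm correlation r between the two changes = 0.3, 0.4 or 0.5. Assumed; the article gives none.
- No causal effect of cognition on functioning, so true mediation is zero.

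**Formula.** With both changes scaled to a within-arm SD of 1, the mediator's coefficient equals r. The adjusted group coefficient is c − r × a, and the shift is r × a.

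| r | shift r × 0.54 | % of c = 0.30 | % of c = 0.50 | % of c = 0.80 |
|---|---|---|---|---|
| 0.3 | 0.162 | 54% | 32% | 20% |
| 0.4 | 0.216 | 72% | 43% | 27% |
| 0.5 | 0.270 | 90% | 54% | 34% |

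For c = 0.50 the adjusted coefficient is 0.338, 0.284 and 0.230.

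**Second check, by simulation** (400,000 subjects per scenario, parameters assumed). T is group, M mediator change, Y functioning change and U a shared cause: M = 0.54T + uU + error, Y = cT + bM + uU + error. Here c is the direct effect only. M has within-arm SD 1, and the error in Y has SD 1.

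| Scenario | b | c | u | true total | true indirect | adjusted group coefficient | total minus adjusted |
|---|---|---|---|---|---|---|---|
| Full mediation | 0.4 | 0 | 0 | 0.216 | 0.216 | 0.00 | 0.22 |
| Partial mediation | 0.4 | 0.2 | 0 | 0.416 | 0.216 | 0.20 | 0.22 |
| No effect, shared cause | 0 | 0 | 0.5 | 0 | 0 | −0.14 | 0.14 |
| Direct effect only, shared cause | 0 | 0.2 | 0.5 | 0.20 | 0 | 0.07 | 0.14 |

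The model without the mediator recovered the true total in every scenario, to within simulation error. In the first row the benefit is real and the adjusted coefficient shows none. In the last two rows there is no mediation, yet the difference between the two coefficients suggests an indirect effect of 0.14.

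**The case against.** The strongest reply is that the aim is mechanism, not efficacy. A model of functioning on group plus mediator is a standard component of a mediation analysis, and the primary model supplies the path from treatment to cognition. An indirect effect could be assembled from the two. This stands in part: the model is a usable component. But the assembly needs an assumption of no unmeasured mediator–outcome confounding. The article states neither that assumption nor an indirect effect, and presents the adjusted model as the analysis that follows from the hypothesis.

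Several stronger readings are tempting, and the document does not support them:
- *Functioning will be compared only after mediator adjustment.* This is the only functioning model with a treatment term in the article, but an analysis plan that is not shown may hold another.
- *The two changes are concurrent.* Assessments usually share a session, but Statistical approach does not say which visits are paired, so a lagged pairing is not excluded.
- *Mediation will be declared when the coefficient shrinks, and clinical mediation dismissed when non-significant.* No decision rule is written.
- *A real benefit will be understated.* That follows only if the adjusted coefficient is presented as the treatment effect. The text is open about the adjustment.
- *Bridging sessions given only in the CR arm make the bias worse.* The shift r × a does not depend on the direct path, and a larger direct effect makes the percentage smaller.

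It is also fair that any single percentage depends on an invented functioning effect. The effect is therefore varied above.

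**Conclusion.** The point holds for the model as written. Its group coefficient is a conditional direct effect. It does not estimate what CR does to functioning, and alone it cannot show that cognitive rather than clinical change mediates.

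Under the stated assumptions (cognitive effect 0.54 SD, residual correlation 0.3 to 0.5, no true mediation) the coefficient moves by 0.16 to 0.27 SD. The percentage depends heavily on the assumed functioning effect: from 20% (0.80 SD, r = 0.3) to 90% (0.30 SD, r = 0.5). The downward direction needs only a positive effect of CR on cognition and a positive residual correlation between the changes.

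This should be changed before analysis, but it touches the secondary aim only. The primary cognition analysis and the sample size stand as they are.

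**What to change.** 1. **Total effect.** Analyse MCAS and SOFAS with a mixed model of the primary type: group and group-by-time, the baseline score of that scale as covariate, no mediator. Report this as the effect of CR on functioning.
2. **Mediation, as a separate analysis.** Enter cognitive and clinical change together, adjusting for baseline cognition, functioning and symptoms. Report each indirect effect, and the difference between them, with bootstrap intervals. State the assumption of no unmeasured confounding, and add a sensitivity analysis for residual correlation between mediator and outcome.
3. **Supporting analysis.** Repeat step 2 with mediator change measured before the functioning outcome, for example change to post treatment and functioning at 6 months. Time order helps against reverse causation but does not remove shared causes. It also sets aside earlier functioning data, so it should not be the sole analysis.
4. **Wording of the conclusion.** Judge the cognitive-but-not-clinical claim by the estimated difference and its interval, not by one result being significant and the other not.

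The cost is analysis text and some extra analysis. The existing schedule of four assessments supplies the data. The real limit is precision: with 100 × 0.85 = 85 completers, intervals for the indirect effects, and above all for their difference, will be wide, and the report should say so.

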## Discussion

The present study is the first we are aware of to implement an Internet-based CR paradigm in patients with BDP and to develop a comparable Internet-based control. The hybrid online/study site format allows accessible treatment while providing opportunities for staff contact and bridging. Our newly developed web-based control is comparable to the treatment in terms of administration and interface: it is dose-matched, including requirements for in-person visits and study staff contact; administrator oversight permits adherence monitoring; sessions are similar in format to those of the CR paradigm.

Based on preliminary feedback from our feedback survey, participant blindness can be successfully maintained with our present paradigm. Responses from the first 22 participants to complete the survey showed that subjects did not differ in terms of which condition they believed they were randomized to: 86 % of subjects in the treatment and 63 % of subjects in the control reported believing that they had participated in the active CR treatment (Chi^2^ = 1.56, *p* = 0.20). On a three-point scale evaluating confidence in their belief of their reported assignment (very (3), somewhat (2), or not at all (1)), participants had low confidence in their ratings in both treatment and control conditions (mean = 1.64, SD = 0.63 and mean = 1.63, SD = 0.92, respectively; *t =* 0.05, *p* = 0.96). Our newly developed active control permits examination of specific elements of our CR paradigm by accounting for many of the nonspecific elements of participation in the study while maintaining the participant and assessment staff blind.

Ultimately, our primary aim is to evaluate efficacy of this CR program compared to active control. We also aim to examine predictors of treatment adherence and response, and neurobiological mechanisms of action using magnetic resonance imaging (MRI) techniques. Better understanding of both predictors of treatment response and the mechanisms of action of CR will allow further refinement and individualization of treatment efforts. We will also be able to examine the role of baseline characteristics, reward processing, and neurobiological response in the relationship between cognitive and functional outcomes.

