**Discussion:**

The present study is the first we are aware of to implement an Internet-based cognitive remediation program in patients with bipolar disorder with psychosis and to develop a comparable web-based control paradigm. The mixed online and study-site format allows accessible treatment while providing weekly staff contact and bridging. Based on user-provided feedback, participant blinding is feasible.

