#### Feedback survey

A user feedback survey was created by our group to evaluate participants’ experiences using the CR or control activities, and to evaluate participants’ beliefs about their study assignment to test the effectiveness of the blind. The first 13 items ask about tolerability, including enjoyment of the tasks, especially compared to other types of treatment, perception of difficulty, stressfulness of the activities, feelings of competency generated by participation, and whether users would continue to participate if given the option. Responses are given using a Likert scale (1–5) with higher scores indicating stronger response; 4 of the 13 items inquired about negative experiences such that higher scores were associated with more negative responses; these items were reverse scored so that in all cases a higher score indicates more positive response. Cumulative scores range from 13 to 65. Subjects were also asked in a forced-choice item to indicate which treatment condition they believed they were assigned to, and then asked to rate the certainty of their selection.

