### Limitations

While extensive efforts will be made to minimize missing data, attrition is a major concern in long-duration CR paradigms. We have implemented several techniques for minimizing attrition including monetary bonuses for reaching session milestones (awarded after 10 sessions, 30 sessions, and 50 sessions, in increasing amounts), regular phone and email contact from study staff reminding subjects to complete sessions at home, weekly in-person visits, and weekly session tracking feedback that displays progress and time to next bonus graphically. However, attrition remains a concern. Thus, for all analyses we will use statistical methods that incorporate partially observed data, and assess the sensitivity of results to different assumptions about the mechanism by which data are missing.

In any clinical trial the potential for bias in recruitment or allocation is a concern. All potential subjects meeting enrollment criteria are offered the opportunity to participate; special efforts will be made to ensure that the enrollment of women and minorities matches the demographics of the region. Allocation is done using a blocked random design based on number sequence, without consideration of participant characteristics. Thus, the main source of bias in this study is likely in non-random characteristics of participants who do or do not adhere to the study procedures. As noted above, we will use statistical methods to minimize the potential for such post-randomization bias.

In terms of masking, we have developed an approach that maximizes our ability to include blinding of participants and study staff; however, as noted above, while assessment staff are able to remain blinded to study assignment, due to the nature of the intervention treatment staff are not. Thus, there is the potential for information about group membership to inadvertently become known to participants or to assessment staff. Because poor masking of treatment allocation is associated with potential inflation of treatment effects [21], the issue of blinding in treatment studies is of key importance. Our post-treatment feedback survey suggests that we have been able to maintain participant blinding, but the potential for a break in the blind remains a limitation.

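### A non-significant test in 22 survey completers is read as showing that participant blinding holds, but the data are inconclusive

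*Protocol article*

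**What the plan says.** The Feedback survey section describes the instrument: "Subjects were also asked in a forced-choice item to indicate which treatment condition they believed they were assigned to". A second item records how certain they were. The Procedures section says these two items help to determine whether the blind was kept.

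The Discussion gives early results from 22 survey completers. It states that "subjects did not differ in terms of which condition they believed they were randomized to". The figures behind this are 86% in the CR arm and 63% among controls who thought they had been given active CR ("Chi^2^ = 1.56, *p* = 0.20"). Mean certainty on a three-point scale was 1.64 (SD 0.63) in the CR arm and 1.63 (SD 0.92) in the control arm, p = 0.96. The conclusion is that "participant blindness can be successfully maintained with our present paradigm".

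The abstract says "Based on user-provided feedback, participant blinding is feasible". The Limitations section is more guarded: "Our post-treatment feedback survey suggests that we have been able to maintain participant blinding". It adds that the blind may nevertheless have been broken.

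**The concern.** A non-significant test in a very small sample is taken as evidence that the arms hold the same beliefs. No interval and no margin for an acceptable difference is given, so the reader cannot see how large a difference the data leave open.

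This is more than a side remark. The Background lists assessment of the design's ability to stay blinded as the third aim of the report, and the Limitations section says that poor masking can inflate treatment effects. A reader who takes the statement at face value would treat one important source of bias as ruled out when it has not been.

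**Working it through.** **Inputs.** From the Discussion: 22 respondents, 86% (CR) and 63% (control) believing they had CR, chi-square 1.56, p = 0.20, and the certainty means and SDs. Arm sizes are not printed.

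**Step 1: recover the table.** Going through every split of 22 into two arms and every count within each arm, only one combination rounds to 86% and 63%: 12/14 = 85.7% and 5/8 = 62.5%.

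| | Believed CR | Believed control | Total |
|---|---|---|---|
| CR arm | 12 | 2 | 14 |
| Control arm | 5 | 3 | 8 |
| Total | 17 | 5 | 22 |

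**Step 2: reproduce the printed test.** Uncorrected chi-square = 22 × (12×3 − 2×5)² / (14 × 8 × 17 × 5) = 22 × 676 / 9,520 = 1.562, p = 0.21. The statistic matches. The printed p of 0.20 is 0.01 low, which is immaterial. Arm sizes of 14 and 8 also return the printed t of 0.05 and p of 0.96 for certainty when the unrounded means 23/14 and 13/8 are used.

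**Step 3: check whether the test suits the table.** Expected counts for believing control are 14 × 5/22 = 3.18 and 8 × 5/22 = 1.82. Two of the four cells are below 5, so an exact test is the better choice: Fisher p = 0.31.

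**Step 4: estimate the difference.** 85.7% − 62.5% = 23.2 points. Newcombe's method combines the Wilson limits of each arm (CR 60.1% to 96.0%; control 30.6% to 86.3%):

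- lower: 0.232 − √[(0.857 − 0.601)² + (0.863 − 0.625)²] = −0.12
- upper: 0.232 + √[(0.960 − 0.857)² + (0.625 − 0.306)²] = +0.57

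The 95% interval is −12 to +57 points.

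**Step 5: see how lenient the criterion is.** With CR held at 12/14 and only 4 of 8 controls believing they had CR, the gap would be 36 points and the same chi-square would still be non-significant (p = 0.07).

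**Step 6: look at each arm.** Correct guesses were 12/14 in the CR arm (86%, exact 95% CI 57% to 98%) and 3/8 in the control arm (37.5%, exact 95% CI 9% to 76%). Overall, 15/22 were correct (exact p = 0.13 against 50%).

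**Step 7: look at certainty.** On a scale of 1 to 3, the printed means and SDs fit one distribution per arm.

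| | Not at all | Somewhat | Very |
|---|---|---|---|
| CR arm (14) | 6 | 7 | 1 |
| Control arm (8) | 5 | 1 | 2 |

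Half of the respondents (11 of 22) had no confidence in their guess. Yet 8 of 14 in the CR arm were at least somewhat certain, and 2 of 8 controls were very certain. Equal means do not show that the guesses were uninformed.

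**The case against.** The best defence is that the text is hedged and does not rest on the chi-square alone. The Discussion calls the feedback preliminary, the Limitations section says only that the survey suggests blinding held, and certainty was low and nearly equal between arms. The planned efficacy analysis is not affected. The hedges do count, and the criticism applies to the Limitations section only weakly. They do not cover the abstract, nor the statement in the Discussion that the arms did not differ. The certainty ratings add some reassurance but, as step 7 shows, do not decide the question.

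A reader might go further and infer that CR participants recognised their allocation, because 12/14 against 50% gives an exact p of 0.013. The documents do not support that. A 50% reference assumes no prior leaning to either arm, yet 5 of 8 controls and 17 of 22 respondents overall chose CR. Against the control arm's own rate of 62.5%, 12/14 gives p = 0.10. If CR respondents with no confidence are counted as undecided, 8 remain, and the p-value against chance runs from 0.008 (no wrong guess among them) to 0.29 (both wrong guesses among them).

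A reader might also cite low power for the observed difference. That only restates the p-value; the interval carries the argument. Finally, nothing in the document says that people who stopped early did so because they guessed control, or that the same non-significance criterion will be applied at trial end.

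**Conclusion.** The conclusion is wrong as written in the abstract and the Discussion, and overstated, though hedged, in the Limitations section. A difference of 23 points with a 95% interval from −12 to +57 neither shows that the arms held the same beliefs nor that the blind failed. The pattern fits a general leaning towards active CR as well as recognition of CR, and these data cannot separate the two. They also describe only those who completed the post-treatment survey.

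This rests on arm sizes of 14 and 8, which are inferred but are the only ones that fit the printed percentages, and on the printed percentages being correctly rounded. The point concerns the blinding claim; it changes no endpoint, sample size or planned efficacy analysis.

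**What to change.** - In the abstract and the Discussion, replace the statements that the arms did not differ and that blinding is feasible or can be maintained with a statement that the early data are inconclusive. Bring the Limitations sentence into line.
- Report the counts by arm, the difference with its 95% interval, and an exact test.
- In the final blinding assessment, report the proportion of correct guesses in each arm, or an arm-specific blinding index, with exact 95% intervals and with certainty taken into account. Judge blinding from the intervals, not from a non-significant p-value.
- Give the two existing items also to participants who stop early, at discontinuation, so that the result does not describe completers only.

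The cost is some rewording and two existing questions at discontinuation. The downside is a weaker feasibility claim.
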